## Materials and methods

### Study design

To compare the BP and HW interventions to a waiting list, we plan to carry out a three-arm randomised controlled study, including female students from French-speaking Switzerland. We will recruit 90 participants over a 12-month period, starting in January 2021. Participants will be randomly assigned to one of the three arms of the study. Both interventions are composed of four weekly sessions and last one month. The waiting list duration will be set to one month in a parallel way. Participants will be evaluated before (T0) and after (T1) the interventions or the waiting list. The interventions are given to groups of six participants and will start each time a group is formed following randomisation. Following the interventions, the participants will have one month of follow-up without contact with the investigators before a final evaluation (T2). To maximise the feasibility of the study regarding funding and university calendar, participants in the waiting list group will receive the BP intervention following the one-month waiting period instead of waiting until the end of the follow-up assessments. They will be evaluated at the end of the intervention (T2). The procedure is described in Fig 2.

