### Random allocation

After receiving the consent form, the participant will be randomised into one of the three study arms, with a 1: 1: 1 allocation ratio. Randomisation will be blocked to ensure that groups are of equal size and that groups of six participants for each arm are regularly formed. The blocks will be of variable size (3, 6, 9) to protect the concealment. There is no stratification. The randomisation sequence will be implemented in the REDCap software, so none of the team members will know in advance which arm the next participant will be assigned to.

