### Sample size

To assess the effectiveness of each intervention, we will recruit a sample of 30 participants per arm, for a total N of 90 participants randomised into three groups. This sample size appears sufficient to detect a large pre-post effect on body dissatisfaction (primary outcome) according to data reported in previous studies [36], and including a hypothetical dropout rate of 10%. The effect sizes (Cohen’s d) reported in the Stice studies are large for the BP or the HW and generally exceed 0.50 (e.g. ref. [36] where the effect sizes were 0.90). To capture a pre-post effect of 0.50 with a power of 0.80 and a probability of 0.05, a sample of 27 people is needed for an intervention (calculated with G * Power 3.1 [37]).

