### Interventions

Because of the pandemic situation due to COVID-19, we chose to deliver the interventions virtually via a collaborative platform, in order to keep a group format while preserving a safe distance. To our knowledge, the effectiveness of the BP when delivered virtually has been evaluated by only one Swedish study, the results of which have just been published [26]. The virtually delivered BP intervention preserved its preventive effect in relation to symptoms of eating disorders, restraint, body dissatisfaction, and internalisation of the thin ideal, compared to a placebo condition of expressive writing and a waiting list control condition.

The BP offers discussions and exercises to make participants realise the cost of pursuing social ideals valuing thinness. The exercises proposed in the BP intervention produce cognitive dissonance [38], which is a cognitive discomfort due to a contradiction between speech and beliefs. This discomfort motivates the person to change their beliefs. The curriculum includes discussions on techniques of the advertising industry and the unique ideal of beauty promoted worldwide, as well as on the costs of pursuing the thin ideal. The participants are also challenged to try behaviours they avoid because their appearance bothers them. Societal activism actions are also discussed. The content of the sessions are manualised and can be downloaded from the website www.bodyproejctsupport.org/resources/materials (4-session French Translation).

The HW allows participants to make personalised changes in their diet and physical activity gradually each week to aim for a health ideal rather than a thin ideal. The programme targets small changes, which are based on behavioural change techniques. Advice is given to participants on what types of changes to introduce to promote their health and how to implement changes sustainably. Difficulties are discussed in the group with a problem-solving approach. The last session introduces a long-term view of lifestyle change. The Healthy Weight programme is manualised and the 4-session script can be downloaded from the website: https://healthyweightsupport.weebly.com/healthy-weight.html.

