The two interventions include four 90 minutes sessions given over a month by two facilitators, the principal investigator (IC) or the co-investigator ([name]), and two research assistants. IC and a research assistant will lead all BP sessions and [name] and the second research assistant will lead all HW sessions. The four facilitators were trained to the BP programme by the person who translated the programme into French. They trained themselves on their own to the use of the HW programme. Before starting the study, a dry run of both programmes will be conducted. The sessions will be held on a collaborative platform in groups of six people and will be recorded. The aim of the recordings is to serve as a means of quality control regarding the way in which the interventions are delivered. The quality control will be carried out internally, on randomly selected portions of sessions. The participants will have signed a consent form for the recording of the sessions. No health or confidential data will be discussed during interventions, which makes it acceptable to record sessions. These records will be destroyed once the quality control has been carried out.

To increase participants’ adherence, reminders will be sent to them via e-mails between sessions.

The waiting list will consist of two assessments, each separated by a one-month interval. Following this waiting time, participants will receive the BP intervention because it is the intervention that has achieved the larger effects [21,22]. A third assessment will take place at the end of the intervention.

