### Data management and statistical analysis

Participants will receive a code upon entering the study. Coding will start at 001 and continue with +1. The signed consent form will contain the equivalence between the participant’s contact details and their code. All forms will be printed and stored in a locked drawer. The electronic forms will be stored in a protected space, which will be backed up regularly during the study. At the end of the study, the data will be stored in a repository, which guarantees that archiving and data sharing will be performed in accordance with FAIR principles. The study will be internally monitored.

The questionnaires (validated questionnaires, socio-demographic variables, satisfaction indices) will be implemented in the REDCap software [52], hosted at the HES-SO (University of Applied Sciences and Arts, Western Switzerland), which will be used to collect the data. The participant’s e-mail address will need to be entered in the platform to allow the surveys to be sent, but it will be coded as an identifier and not exported to the database. Only the participant’s code will represent the participant in the final database.

Missing data will be handled with a single imputation method. To test the hypothesis stipulating a pre-post difference between the participants of the two intervention groups and the participants of the control list, analyses of variance (ANCOVA analyses of covariance with time pre in covariate) will be conducted in order to compare the three groups BP, HW, and waiting list on the different dependent variables, with post-hoc analyses to compare the groups two by two. The primary outcome is body dissatisfaction assessed with the BSQ-8C. Similar analyses will be carried out for the secondary outcomes. Regarding the stability of the intervention and the hypothesis predicting that the observed effects will be maintained after one month of follow-up, repeated measures analyses of variance will be performed. The statistical analyses will be carried out with completers and intent-to-treat.

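### BP and HW run in discussion groups of six, but neither the ANCOVA nor the sample size allows for within-group correlation; if it is positive, standard errors are understated

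*Protocol article*

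**What the plan says.** The protocol article fixes four things that bear on this point.

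- **Unit of randomisation.** Under Random allocation, "the participant will be randomised into one of the three study arms, with a 1: 1: 1 allocation ratio".
- **Unit of delivery.** Under Study design, "The interventions are given to groups of six participants and will start each time a group is formed following randomisation". The Interventions section repeats it: "The sessions will be held on a collaborative platform in groups of six people and will be recorded". Each group meets four times for 90 minutes. Interaction is part of both programmes. For BP, "The BP offers discussions and exercises to make participants realise the cost of pursuing social ideals valuing thinness"; for HW, "Difficulties are discussed in the group with a problem-solving approach". The waiting list has two assessments a month apart and starts BP only after T1.
- **Analysis.** Under Data management and statistical analysis, "analyses of variance (ANCOVA analyses of covariance with time pre in covariate) will be conducted" to compare the three arms, followed by post-hoc pairwise comparisons and, for follow-up, repeated measures ANOVA. No group term, random effect or cluster-robust variance is named.
- **Sample size.** The plan states: "To capture a pre-post effect of 0.50 with a power of 0.80 and a probability of 0.05, a sample of 27 people is needed". This number applies to each programme separately. After a 10% allowance for dropout, "we will recruit a sample of 30 participants per arm, for a total N of 90 participants randomised into three groups". No ICC or design effect appears.

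Correlation within discussion groups is not mentioned anywhere in the article.

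**The concern.** Six participants who share four interactive sessions may well finish with more similar outcomes than six participants from different groups. At T1 this can arise in BP and HW but not in the waiting list, so the design is partially nested. An ANCOVA with independent errors counts 30 participants per active arm as 30 independent pieces of information. If the ICC is positive they carry fewer, the standard errors of the arm contrasts are too small, and the test rejects more often than its nominal level. The sample size has no margin for this either.

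This is not a detail merely left to an analysis plan, because the article names the model and gives the whole sample-size derivation. It matters even in a preliminary study: body dissatisfaction is tested as a primary outcome, and the Discussion says the data will support a grant proposal. Overstated precision, with no ICC reported, would carry over into the planning of that next trial.

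**Working it through.** **Inputs from the protocol:** group size 6; 30 per arm, so 30/6 = 5 groups per active arm; pre-post d = 0.50; power 0.80; alpha 0.05 (sidedness not stated); dropout 10%. **Assumed:** the ICC, meaning the correlation within a discussion group of T1 outcomes given T0 (or of pre-post change, for the power calculation). The documents give none, so a range of 0.02 to 0.15 is used.

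**Step 1: reproduce the plan's figure.** Exact noncentral-t power for a paired t-test at d = 0.50 on independent participants gives n = 27 one-sided (power 0.812). A two-sided test would need n = 34 (power at 27 is 0.706). Then 27/(1 − 0.10) = 30. So the stated figure reproduces with a design effect of exactly 1, and the step from 27 to 30 is used up by dropout.

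**Step 2: design effect.** In BP and HW, DE = 1 + (6 − 1) × ICC. In the waiting list at T1, DE = 1.

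**Step 3: true standard error over model standard error.** BP or HW against the waiting list: √((DE + 1)/2). BP against HW: √DE.

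**Step 4: type I error of an unadjusted two-sided 5% test.** The approximation is 2 × [1 − Φ(1.96/ratio)]. It was checked by simulating the planned ANCOVA with 5 groups of 6 in BP and in HW and 30 independent waiting-list participants (20,000 runs and pre-post correlation 0.6 for ICC 0, 0.02, 0.05 and 0.10; separate runs for 0.15).

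| ICC | DE | Effective n of 30 | SE ratio vs waiting list | SE ratio BP vs HW | Type I vs waiting list: formula / simulated | Type I BP vs HW: formula / simulated |
|---|---|---|---|---|---|---|
| 0 | 1.00 | 30 | 1.00 | 1.00 | 5.0% / about 5% | 5.0% / about 5% |
| 0.02 | 1.10 | 27.3 | 1.02 | 1.05 | 5.6% / 5.4% | 6.2% / 6.1% |
| 0.05 | 1.25 | 24 | 1.06 | 1.12 | 6.5% / 6.3% | 8.0% / 7.9% |
| 0.10 | 1.50 | 20 | 1.12 | 1.22 | 8.0% / about 8% | 11.0% / 11.1% |
| 0.15 | 1.75 | 17.1 | 1.17 | 1.32 | 9.5% / about 10% | 13.8% / about 13% |

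The zero row shows that the excess comes from the grouping and not from the ANCOVA itself.

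**Step 5: power on the plan's own basis.** Keep the one-sided pre-post test at d = 0.50 and replace 27 by 27/DE.

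| ICC | 27/DE | Power | Analysed n that restores the plan's basis (27 × DE, rounded up) |
|---|---|---|---|
| 0 | 27 | 0.81 | 27 |
| 0.02 | 24.5 | 0.78 | 30 |
| 0.05 | 21.6 | 0.73 | 34 |
| 0.10 | 18 | 0.65 | 41 |
| 0.15 | 15.4 | 0.59 | 48 |

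These powers are somewhat optimistic, because with about five groups per arm the correct test also has few degrees of freedom. In the other direction, 10% dropout lowers the mean analysed group to 5.4, so DE at ICC 0.05 and 0.15 is about 1 + 4.4 × 0.05 = 1.22 and 1 + 4.4 × 0.15 = 1.66.

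**The case against.** Several points limit the concern.

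- **The ICC is unknown.** A reader might infer that the intervals are certainly too narrow and that the false-positive rate exceeds 5%. The documents do not support that. Individual randomisation removes systematic pre-existing differences between groups, so any ICC has to arise from one month of shared sessions. At ICC 0.02 the error against the waiting list is only about 5.5%. This stands, and the conclusion must be conditional.
- **The largest figures are not for the hypotheses.** The second hypothesis compares each intervention with the waiting list. BP against HW enters only as one of the post-hoc pairs. This stands, so the waiting-list figures should lead.
- **The figures assume unadjusted tests.** The protocol does not name its post-hoc method. Under Bonferroni over three pairs (level 1.67%), the formula in Step 4 with 2.394 in place of 1.96 gives about 2.4%, 3.2% and 4.1% against the waiting list at ICC 0.05, 0.10 and 0.15. These are below 5% but still above the level that the adjustment aims at.
- **Sixes are formed in every arm.** Random allocation says so, but waiting-list participants share no session before T1, so partial nesting remains the right reading at T1. By T2 they too have had BP in groups.
- **Very large effects would survive.** As an illustration, take the cited 0.90 as a between-arm effect with 27 per arm. Then t = 0.90/√(2/27) = 3.3. At ICC 0.10 it is 0.90/√(1.5/27 + 1/27) = 3.0, still above a Satterthwaite critical value near 2.2. Borderline results are the ones at risk. The sample size, however, is set for 0.50.
- **The remedy is hard to estimate.** With about five groups per arm the group variance will be imprecise and may be estimated as zero. This also stands, and it argues for a simple model with small-sample degrees of freedom. It is not a reason to leave the grouping out.

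**Conclusion.** The concern holds in conditional form, as something that should be fixed. The omission itself is certain: the named ANCOVA has no group term, and the sample size reproduces only under independence. The harm depends on a positive within-group ICC, which interactive delivery makes plausible but which the protocol does not quantify. For an assumed ICC of 0.02 to 0.15 and unadjusted 5% tests, type I error is about 5.5% to 10% for the hypothesised contrasts with the waiting list, and about 6% to 13% for BP against HW. The plan's own power of 0.81 at 27 analysed falls to about 0.73 at ICC 0.05 and 0.65 at ICC 0.10. The effect is minor at the bottom of the range and material from about 0.05 upward. Unequal residual variance between arms is not an established fault of the plan.

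**What to change.** - **Analysis.** Analyse T1 with a partially nested mixed model: T0 value as covariate, arm as fixed effect, a random intercept for discussion group in BP and HW only (waiting-list participants treated as singletons), and Kenward-Roger or Satterthwaite degrees of freedom. Arm-specific residual variance can be an optional sensitivity analysis.
- **Data.** Keep a discussion-group identifier in the analysis dataset.
- **Sample size.** Leave enrolment at 90, but restate the power or the detectable effect over a stated ICC range.
- **Reporting.** Give the observed ICC with its interval, for use in the planned grant proposal.

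**Cost.** Revised analysis wording and, if it is not already recorded, one data field. Randomisation, delivery and measures do not change. Intervals will be wider, and with about five groups per active arm the group variance will be estimated imprecisely. The model cannot separate programme from facilitator, because each programme is led by its own pair; that is a separate matter.

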**Fig 2 pone.0259796.g002:**
[figure not shown]
Flowchart illustrating recruitment and assessment of the participants through the study. Adapted from the CONSORT 2010 flow diagram.

### Participants

The target population of the study are female students from the University of Geneva and other French-speaking cantons, and the University of Applied Sciences and Arts Western Switzerland (HES-SO) aged 18 to 25, with body dissatisfaction and a BMI between 18.5 and 30 kg/m^2^. To recruit the participants, a brief video proposing to test an intervention to improve one’s body dissatisfaction will be posted on the universities’ social networks. Students’ associations will be harnessed to convey information on the study.

The inclusion criteria are as follows:

Female student;Aged between 18 and 25 years old;BMI between 18.5 and 30 kg/m^2^;French-speaking (or understands French sufficiently to participate in the intervention) and living in Switzerland for at least six months;Suffers from body dissatisfaction and obtains a score of at least 26 on the BSQ-8C [34], which represents a moderate concern with body image;Accepts the use of a collaborative platform to participate in the intervention group, which implies that her name may be revealed, and accepts that the sessions will be recorded.

The exclusion criteria are:

Eating disorder diagnosis declared according to the DSM-5 diagnostic criteria (past or current);Any diagnosis of mood disorder or anxiety disorder;Pregnancy.

These criteria will be assessed during a first meeting via a phone call or videoconference by one of the members of the project team. If the participant meets the inclusion criteria and shows interest, she will receive the information and consent forms by mail, to be signed and returned. The participants will never be met face to face.

### Withdrawals

In the event that a participant develops an eating disorder during the study, she will be withdrawn from the study and referred to a specialised centre. Unhealthy attitudes and behaviours will be carefully monitored during the interventions by the two facilitators who lead the group sessions, who have both a clinical experience in the field of eating disorders and obesity. If the participant becomes pregnant during the study, she will be excluded, since changes in the body as well as hormonal changes, even in early pregnancy, can influence the results of the questionnaires [35].

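### The withdrawal and pregnancy rules, read as written, end outcome collection after randomisation, which does not fit the promised intent-to-treat analysis and may act unequally between arms before T1

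*Protocol article*

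**What the plan says.** Two rules in the Withdrawals section of the protocol article remove participants after randomisation.

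- Eating-disorder onset: "In the event that a participant develops an eating disorder during the study, she will be withdrawn from the study", with referral to a specialised centre. The removal is from the study, not only from the group sessions.
- Pregnancy: "If the participant becomes pregnant during the study, she will be excluded". The reason given is that bodily and hormonal changes can alter the questionnaire answers.

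On detection, the same section names one route: "Unhealthy attitudes and behaviours will be carefully monitored during the interventions by the two facilitators who lead the group sessions".

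On analysis, Data management and statistical analysis says: "The statistical analyses will be carried out with completers and intent-to-treat". Missing data are to be filled by single imputation, with no method named. The test of effectiveness is an ANCOVA of the three arms on the post-intervention (T1) score, adjusted for the T0 score.

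**The concern.** Intent-to-treat means that every randomised participant is followed and analysed in the arm assigned, whatever happens afterwards. Both rules work against this, in different ways.

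Eating-disorder onset is closely tied to what the trial measures. EDE-Q psychopathology is a secondary outcome, and the Discussion treats body dissatisfaction, the primary outcome, as a proxy for eating-disorder risk. If follow-up ends at onset, scores are missing because the participant worsened.

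Pregnancy is a different case. Nothing suggests that these participants score worst, but a randomised participant is set aside for a later event precisely because that event may affect her measurements.

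Detection adds a possible imbalance. If onset is noticed mainly in sessions, it is noticed before T1 mainly in the Body Project (BP) and Healthy Weight (HW) arms. Worsening participants would then be lost from those arms and kept in the waiting list. That would flatter the interventions and weaken the record of deterioration in an at-risk group.

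**Working it through.** **The plan's own figures.** Sample size gives a pre-post effect of 0.50, power 0.80, probability 0.05, 27 people per intervention and 10% dropout. A one-sided paired t test with n = 27 has power 0.812, and 27 / 0.90 = 30 per arm. (A two-sided test would need 34.) These figures are not in dispute here; n = 30 and the effect of 0.50 serve as the yardstick.

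**Who can be seen by a facilitator, and when.**

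- T0 to T1, BP and HW: four 90-minute sessions (Interventions).
- T0 to T1, waiting list: no sessions; "The waiting list will consist of two assessments, each separated by a one-month interval".
- T1 to T2, BP and HW: follow-up without investigator contact (Study design).
- T1 to T2, waiting list: sessions, since "participants in the waiting list group will receive the BP intervention following the one-month waiting period".

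The named monitoring therefore covers only the active arms before T1 and only the waiting list afterwards. The first interval is the one that matters for the T1 comparison.

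**Effect of removal on an arm mean (assumed inputs).** Let k of 30 worsen by 1 SD while the rest improve by 0.5 SD.

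- k = 1: true mean improvement = (29 × 0.5 − 1 × 1) / 30 = 13.5 / 30 = 0.45 SD. After removal it is 0.50 SD, a shift of 0.05 SD.
- k = 2: (28 × 0.5 − 2 × 1) / 30 = 12 / 30 = 0.40 SD. After removal it is 0.50 SD, a shift of 0.10 SD, which is 0.10 / 0.50 = one fifth of the planning effect.

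Imputing the mean of the remaining participants gives the same 0.50, so the same shifts. Carrying the baseline forward gives (29 × 0.5) / 30 = 0.483 and (28 × 0.5) / 30 = 0.467, shifts of 0.03 and 0.07 SD.

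More generally, removing k participants whose scores are m SD worse than the arm mean shifts that mean by k × m / (30 − k). For m from 1 to 2 this is 0.03 to 0.07 SD (k = 1), 0.07 to 0.14 SD (k = 2) and 0.11 to 0.22 SD (k = 3).

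**Effect on the ANCOVA.** A simulation compared one active arm with the waiting list: 30 per arm, no true effect, assumed pre-post correlation 0.6, two-sided 5% test, 6,000 runs. The k worst T1 scores were lost in the active arm only. With no loss the type I error was 0.048. Cells show spurious benefit in SD, then type I error.

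| Handling | k = 1 | k = 2 | k = 3 |
|---|---|---|---|
| Deleted | 0.04; 0.057 | 0.09; 0.073 | 0.12; 0.098 |
| Arm mean imputed | 0.07; 0.068 | 0.13; 0.106 | 0.18; 0.168 |
| Baseline carried forward | 0.03; 0.059 | 0.05; 0.061 | 0.07; 0.069 |

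Losing exactly the worst scores, in one arm only, is close to the upper end for each k.

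**How many cases?** The documents give no onset rate. Two of 30 is 6.7% within one month, in a group screened for past or current eating disorders. The Introduction gives a lifetime figure of 17.5% for Swiss women, summed over several categories; 6.7 / 17.5 is over a third of it. One of 30 is 3.3%. Two is thus an extreme case, and none is quite possible.

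**The case against.** The strongest defence is that being withdrawn from the study is not the same as being dropped from the analysis. A reader might infer that the protocol deletes these participants from the intent-to-treat set. It does not say so, and imputation could keep them in. It also does not say in so many words that their questionnaires stop, and an article may leave such detail to the full protocol. This stands in part. But the article does state the removal rule, its plain reading ends follow-up, and no analysis plan can recover answers that were never collected.

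Four other stronger readings are tempting and are not supported.

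- That both rules remove the worst outcomes. This has no basis for pregnancy, where the protocol gives no direction. For onset it is likely on the EDE-Q, but the protocol does not state it for the BSQ-8C.
- That detection is possible only in the active arms. Facilitator monitoring is the only route named, but the withdrawal rule covers every participant, self-report is open to all, and all arms complete the EDE-Q at T0, T1 and T2. A case first seen in the T1 EDE-Q already has T1 data. Interventions also says that no health data will be discussed in sessions, so these may reveal few cases.
- That imputation must favour the interventions. The method is unnamed, and the bias differs by method, as the table shows.
- That worsening vanishes from the results. Worsening short of a disorder triggers no withdrawal, the EDE-Q and behaviour frequencies are collected in every arm, and the participant flow figure was not available to check how withdrawals are reported.

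**Conclusion.** The concern holds in a limited form and should be corrected. Both rules, as worded, sit badly with the promised intent-to-treat analysis: one makes outcomes missing for a reason related to the outcome, and the other excludes randomised participants for a post-randomisation event. Unequal removal before T1 is possible, and its probable direction favours BP and HW, but neither is certain.

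The size cannot be known from the documents. Under the assumed changes (1 SD worse against 0.5 SD better, removals in one arm only), it is about 0.05 SD for one case and 0.10 SD for two. With one case or none the practical effect is small. The reason to act is that the loss cannot be repaired later, while preventing it is cheap.

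**What to change.** Leave the clinical referral rule as it is, and make these changes to the wording around it.

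- In Withdrawals, state that referral or stopping the sessions does not end data collection. Send the T1 and T2 REDCap questionnaires to every randomised participant who agrees to continue.
- In the analysis section, state that the intent-to-treat analysis includes every randomised participant in the arm assigned, including those with eating-disorder onset or pregnancy.
- Report eating-disorder onset, pregnancy and withdrawals, with reasons, by arm. The EDE-Q, collected in all arms at the same time points, gives a description of worsening that does not depend on facilitator contact.
- Replace the pregnancy exclusion in the main analysis with a sensitivity analysis that leaves out pregnancy-affected scores.

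The cost is a few sentences, a change to the consent information and a few extra automated surveys. The downside is that a few pregnancy-affected scores stay in the main analysis; the sensitivity analysis shows whether they matter.
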